##### Medical management arm data

As a pragmatic trial using standard treatment as part of the medical management arm, precise assessment of any mometasone furoate spray and Sterimar spray residuum will not take place. Participant compliance with the IMP does not form part of the trial monitoring plan. Participants will be asked at the 6-month follow-up visit (visit 2) to estimate how many bottles of the Sterimar and mometasone furoate spray they used.

Site nursing staff will record details of concomitant medication and any AEs during a phone call at 2 weeks post randomisation and at all scheduled trial visits.

#### Data handling and record keeping

Data will be handled, computerised, stored and archived in accordance with the General Data Protection Regulation (2018), and the latest Directive on Good Clinical Practice (GCP) (2005/28/EC). Patient-identifiable data will remain at each site and not be collected as part of the trial dataset. Patient identification on data collection tools used during screening will be through a unique sequential screening number allocated by site staff. Patients recruited to the main trial will additionally be identified by a unique trial identifier number generated by the randomisation system. Data will be transcribed and NPR files uploaded by site staff to the trial’s secure, password-limited, validated MACRO™ database (Elsevier).

The participant trial record, including completed paper data collection tools, will be archived at site for 5 years following the end of the trial. Audio-recordings will be archived for 10 years.

#### Trial compliance and withdrawal

The trial will be conducted in accordance with the Medicines for Human Use (Clinical Trials) Regulations 2004 and subsequent amendments. All parties must abide by these regulations and the International Conference on Harmonisation-Good Clinical Practice (ICH-GCP) guidelines.

Participants who withdraw their consent from the trial, or are withdrawn by the investigator, will not be replaced. All data collected up until the point of withdrawal will be retained for NAIROS research purposes, and consent will be sought for this (Additional file 2).

#### Sample size calculations

The SNOT-22 Minimal Clinically Important Difference (MCID) in the National Comparative Audit of Surgery for Nasal Polyposis and Chronic Rhinosinusitis was 8.9 [23]. Septal surgery is reported variously as showing reductions in total SNOT-22 scores above (10 points) [29] or below (4 points) this boundary [25]. In the absence of a specific figure for septoplasty MCID, NAIROS has assumed a clinically relevant reduction being at least 9 points.

Reported standard deviations (SD) of the SNOT-22 score were 18 [27] (in external septoplasty) to 24 [28] in septorhinoplasty, NAIROS assumed the larger, more conservative SD.

Sample size calculations were based on a *t* test for superiority assuming equal variance across groups, a conservative estimate given the primary analysis is based on adjustment for stratification covariates, increasing power. The target recruitment of 378 participants allows for 20% drop-out – based upon experience from our unit’s two prior septal surgery audits [10, 39]. The remaining 302 participants (151 per arm at completion), are required to show a 9-point [23] difference in overall SNOT-22 score between arms, with 90% power and 5% Type I error, assuming a SD of 24.

#### Statistical analyses

##### Primary outcome

The primary analysis is comparison of SNOT-22 scores at 6 months by randomised treatment arm (immediate surgery vs medical management). Mean overall scores will be presented by treatment group. The associated significance of any observed difference will be calculated in multivariable regression models adjusting any treatment effect by stratification factors, gender and NOSE severity at baseline. Secondary analysis of the primary outcome measure will adjust for the influence of baseline severity SNOT-22 score as a continuous covariate, planned turbinate reduction as a binary covariate and other important demographic and clinical covariates at randomisation (including, but not exclusively, age, body mass index (BMI), smoking, endoscopic features). Non-linear relationships between continuous baseline measures and outcome will be addressed by simple, and possibly more complex, fractional polynomial transformations.

The NAIROS model will generate a linear predictor score of patient outcome weighted according to the statistical importance of each covariate. Each patient’s linear predictor score will be compared against observed score for internal validation. This model will be used to explore recommendations for treatment options.

The importance of baseline severity, as a continuous distribution of NOSE score at randomisation, may be further explored graphically by Subpopulation Treatment Effect Pattern Plots (STEPP analysis) [40] to display the predicted point estimates of any treatment effect (with 95% CI) over the range of NOSE values (range 30–100 in NAIROS participants), further informing any patient selection guidance and recommendations.

Primary statistical analyses will be carried out on an intention-to-treat basis. The number of ineligible participants and reasons for ineligibility will be reported. A sensitivity analysis may be conducted and reported if the number of ineligible participants or participants not receiving the allocated treatment is excessive. Participants may choose to discontinue the treatment to which they have been allocated, and may also ask that they receive an alternative treatment as per local standard NHS care. The implication of such treatment adjustments, which typifies surgical trials, is that the intention-to-treat analysis will produce a conservative estimate of the effect of septoplasty. Non-compliance (including receiving the alternative treatment) may be addressed using an ‘as treated’ approach or complier average causal effect (CACE) approach, since the intention-to-treat analysis under non-compliance is biased when the intervention effect is large [41]. Statistical methods for withdrawal of participants, based on statistical censoring, may be considered.

Tests of heterogeneity will assess robustness of the overall treatment effect across stratification subgroups, and by intention to perform unilateral turbinate reduction.

There are no formal interim analyses of the primary outcome measure and there are no formal statistical stopping rules. Decisions regarding continuation of the trial will be made at DMC meetings held every 6 months. Decisions will be made on the basis of information presented in a statistical report that includes analysis of formal data snapshots, including safety data.

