##### Screening

Screening data used to assess eligibility will include:
Clinical examination (including nasal endoscopy)Nasal Obstruction Symptom Evaluation Scale (NOSE) score – confirmation of total ≥ 30AgeBaseline recording of four core features at endoscopy of the undecongested nose
◦ The side of the maximum convexity◦ One main site of deflection on each side – anterior/ posterior/upper/lower/all)◦ Confirmation that there is no excluding inflammatory process – pus/polyps/adenoids◦ Magnitude of observer-rated airway block (< 50%; ≥ 50%)

If the participant is unable to complete the endoscopic examination without topical preparation, it can be performed after the airway assessment of the decongested nose.

The NOSE scale is a validated five-item, unifactorial self-report of nasal-block severity which has been applied in previous research and audit studies [21, 22]. The three recognised NOSE-derived categories of baseline severity used will be: 30–50 = Moderate, 55–75 = Severe, 80–100 = Extreme [22].

For NAIROS, it is anticipated that baseline severity will be the most important determinant of outcome. Those with a NOSE score of less than 30 will be excluded from NAIROS on the basis of having symptoms that are too mild to warrant inclusion.

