##### Randomisation

At the baseline visit, consenting, eligible patients will be randomised on a 1:1 basis using random permuted blocks of variable length. Stratification will be by gender and baseline severity (NOSE score).

Randomisation will be administered centrally by the Newcastle Clinical Trials Unit (NCTU) web-based system. The treatment allocation is open label and the randomisation system will provide a unique trial identifier for each participant via email to a delegated member of site staff.

Participants will be randomised between:
Septoplasty with or without unilateral turbinate reductionMedical management

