##### Assessments pre-randomisation

Eligible patients who consent to participate in the main trial will have the following outcome measures administered prior to randomisation:
SF-36 questionnaire (1-week recall version)SNOT-22 questionnaireNasal patency measurements (pre and post nasal decongestant):
◦ PNIF◦ NPRDouble Ordinal Airway Subjective Scale (DOASS)

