##### Analysis of secondary outcomes

Analyses of secondary outcomes will follow a broadly similar strategy. These will include the data at 6-month follow-up from the other outcomes (SNOT-22 subscales, NOSE, DOASS, SF-36) and that for all outcomes at 12-month follow-up.

Subjective scales, tabulated by arm and overall at randomisation, 6-month and 12-month follow-ups, will be compared by both summary statistics and graphical representation. Multiple regression will be used to investigate longitudinal outcome scores between treatment groups at follow-up time points. Variation between participants will be included as a random effect with an assumed normal distribution. Analysis will include the stratification factors of baseline severity and gender. Further adjusted analyses will include terms for baseline values of the scores and key demographic and clinical covariates.

Adverse events will be tabulated according to World Health Organisation (WHO) Common Terminology Criteria for Adverse Events (CTCAE) grade version 4.03. Number of severe (CTC grade 3, 4 or 5) will be reported as a proportion of all AEs. Number of participants experiencing at least one severe CTCAE will be reported as a proportion of all participants. Surgical complication/failure and re-intervention will be tabulated and will not subject to statistical testing. Technical failures from operations where widening of nasal airway was achieved yet the symptoms persist will be reported.

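### The primary model omits baseline SNOT-22, the outcome's own pre-randomisation measurement; the analysis remains valid but gives up precision and protection against chance imbalance

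*Protocol article*

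**What the plan says.** In the Protocol article, Statistical analyses, Primary outcome: "The primary analysis is comparison of SNOT-22 scores at 6 months by randomised treatment arm". Significance is to be assessed in "multivariable regression models adjusting any treatment effect by stratification factors, gender and NOSE severity at baseline". The baseline value of the outcome is placed one tier down: "Secondary analysis of the primary outcome measure will adjust for the influence of baseline severity SNOT-22 score as a continuous covariate". The same sentence adds planned turbinate reduction and further demographic and clinical covariates, in a list described as not exhaustive. Fractional polynomials may be used for continuous baseline measures.

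Under Assessments pre-randomisation: "Eligible patients who consent to participate in the main trial will have the following outcome measures administered prior to randomisation". SNOT-22 is on the list that follows.

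Randomisation is stratified by gender and baseline NOSE score, not by SNOT-22. The Screening section gives the NOSE severity bands as "30–50 = Moderate, 55–75 = Severe, 80–100 = Extreme".

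Under Analysis of secondary outcomes, the main longitudinal model carries the stratification factors, and baseline scores come later: "Further adjusted analyses will include terms for baseline values of the scores and key demographic and clinical covariates".

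**The concern.** The baseline of a continuous patient-reported score is usually among the strongest predictors of its later value. Here it is planned for every randomised participant, yet the model that produces the headline result does not use it. This is a stated allocation of the covariate to the secondary tier, not a detail left open for the statistical analysis plan.

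NOSE severity in the primary model is only a partial substitute. The article describes NOSE as a five-item, single-factor scale of nasal blockage. SNOT-22 also has sleep, ear/facial pain and psychological subscales, and the Primary outcome measure section reports that patients' symptoms mapped better to SNOT-22 than to NOSE.

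Two things are at stake. The primary confidence interval is wider than it needs to be. And in the one randomisation that the trial will have, any chance difference between arms in the unexplained part of baseline SNOT-22 carries over into the primary estimate, multiplied by the baseline-to-outcome slope.

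**Working it through.** **Inputs from the article** (Sample size calculations): difference 9 points, SD 24, 5% type I error, 90% power, 151 per arm analysed (302), 378 recruited with 20% drop-out. Sidedness is not stated; two-sided 5% reproduces the stated size, whereas one-sided 5% would need only about 122 per arm.

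**Inputs assumed, because the article does not give them:**
- *r*, the partial correlation of baseline with 6-month SNOT-22 given gender and NOSE severity: 0.3 to 0.5.
- The share of 6-month variance explained by the stratifiers: 0% or 10%.
- Baseline SNOT-22 SD: 24.
- Slope of 6-month on baseline SNOT-22: 0.5.

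**Step 1: reproduce the stated size.** A two-sided, two-sample *t* test with standardised difference 9/24 = 0.375 needs 150.4, so 151 per arm. Power at 151 per arm is 90.1%. Recruitment is 302/0.8 = 377.5, so 378. The plan's figures are correct.

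**Step 2: the planned primary model.** It already adjusts for the stratifiers, so the fair comparator is not always the unadjusted *t* test. If the stratifiers explain 10% of the variance:
- residual SD = 24 × √0.9 = 22.8
- SE of the treatment difference = 22.8 × √(2/151) = 2.62
- half-width = 1.968 × 2.62 = 5.16 (*t* quantile on 300 df)
- power for 9 points is about 93%

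**Step 3: add baseline SNOT-22.** The residual SD is multiplied by √(1 − r²), which is 0.954 at r = 0.3 and 0.866 at r = 0.5. The SE therefore falls by about 5% or 13%.

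| Variance explained by stratifiers | Model | SE | 95% CI half-width | Power |
|---|---|---|---|---|
| 10% | as planned | 2.62 | 5.2 | about 93% |
| 10% | plus baseline, r = 0.3 | 2.50 | 4.9 | about 95% |
| 10% | plus baseline, r = 0.5 | 2.27 | 4.5 | about 98% |
| 0% | as planned | 2.76 | 5.4 | 90.1% |
| 0% | plus baseline, r = 0.3 | 2.63 | 5.2 | 92.6% |
| 0% | plus baseline, r = 0.5 | 2.39 | 4.7 | 96.3% |

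**Step 4: chance imbalance among completers.** The SE of the between-arm difference in mean baseline SNOT-22 is at most 24 × √(2/151) = 2.76 points. Stratification on NOSE reduces it: if gender and NOSE severity explained 30% of baseline variance, it would be 2.76 × √0.7 = 2.31. At slope 0.5, a one-SE imbalance shifts the primary estimate by up to 0.5 × 2.76 = 1.4 points (1.2 with the 30% reduction), against a 9-point target.

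**The case against.** The strongest reply is that nothing here is invalid. The primary model is pre-specified and adjusts for exactly the factors used to stratify randomisation. It is unbiased over randomisations and keeps its type I error. The trial was sized on an unadjusted *t* test, so none of the promised power depends on baseline SNOT-22. Baseline severity is not ignored, since NOSE severity is both a stratifier and a covariate. An analysis with baseline SNOT-22 is already planned, so the change mainly reorders the tiers. All of that stands, and it makes this a matter of efficiency rather than an error.

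Some stronger readings are tempting but not supported:
- *That the trial is underpowered or its sample size wrong.* Step 1 shows that it is not.
- *That the plan leaves open which analysis prevails if they disagree.* It does not: one is labelled primary and the other secondary.
- *That a baseline imbalance passes in full into the estimate.* Only the slope times the part not explained by gender and NOSE does.
- *That power rises from 90.1%.* That starting point holds only if the stratifiers explain nothing. The article itself calls the *t*-test calculation conservative because of the stratifier adjustment.
- *That every secondary scale lacks its own baseline in its main model.* For NOSE, the baseline severity stratifier supplies it in part.

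The existing secondary analysis does not fully answer the point. It combines baseline SNOT-22 with an open-ended covariate set, so the article defines no fixed model with just the stratifiers and the baseline score. The better use of the baseline therefore sits in the less tightly specified analysis.

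**Conclusion.** The point holds as a weakness of precision and of conditional bias, meaning bias given the imbalance actually observed. It is not a fault of validity or sample size. Under the assumptions shown, the change would narrow the primary interval by about 5% to 13% and add roughly 2 to 6 percentage points of power. The gain is smaller where the stratifiers already explain some of the variance. It would also remove a possible shift of up to about 1.4 points for a one-SE baseline imbalance.

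Confidence is high on what the article says and on the direction of the effect. The size is illustrative, because the correlation, the slope, the baseline SD and the variance explained by the stratifiers are all assumed. The change is worth making because its cost is one degree of freedom out of about 300. The article's own sample size section already accepts that covariate adjustment increases power.

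**What to change.** Before analysis, amend the Primary outcome text under Statistical analyses, and the statistical analysis plan to match:
- **Primary:** 6-month total SNOT-22 regressed on arm, gender, baseline NOSE severity and baseline total SNOT-22 as a continuous covariate.
- **Sensitivity:** the present model with the stratifiers only.
- **Secondary:** the wider covariate model, as now.

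Under Analysis of secondary outcomes, put each scale's own baseline score in its main model. For NOSE, the severity stratifier already does this in part, so state how the baseline score and the stratifier will be handled together.

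The cost is a wording change. It needs no new data collection and no change in sample size.

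### The primary model appears to adjust for baseline NOSE only by severity band; adding the exact score already collected would gain a little precision at almost no cost

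*Protocol article*

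**What the plan says.** In the protocol article, under Statistical analyses – Primary outcome, the treatment comparison comes from multivariable regression "adjusting any treatment effect by stratification factors, gender and NOSE severity at baseline". NOSE thus enters as a stratification factor. The Randomisation section names gender and baseline severity (NOSE) as the two factors, with permuted blocks. The Screening section defines severity: "The three recognised NOSE-derived categories of baseline severity used will be: 30–50 = Moderate, 55–75 = Severe, 80–100 = Extreme". The same section says that "it is anticipated that baseline severity will be the most important determinant of outcome".

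Continuous use is marked where it is meant. Baseline SNOT-22 is called a continuous covariate, but only in the secondary analysis of the primary outcome. NOSE is considered "as a continuous distribution of NOSE score at randomisation" only for an optional graphical (STEPP) exploration. The sentence on the primary model has no such marker.

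Sample size calculations rests on a t test and describes this as "a conservative estimate given the primary analysis is based on adjustment for stratification covariates, increasing power".

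**The concern.** If NOSE enters the primary model by band, participants scoring 30 and 50 are treated as alike, while those scoring 50 and 55, one scale step apart, are treated as different. The total score is known for everyone because eligibility depends on it. Any relation between NOSE and outcome inside a band stays in the residual, and chance imbalance between arms within bands is not corrected. The protocol itself expects this covariate to matter most and expects adjustment to add power, so it is reasonable to ask how much of that gain the banding gives up. What is at stake is the width of the confidence interval for the main result, not its validity.

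This is a separate matter from whether baseline SNOT-22 belongs in the primary model. It concerns only the form of a covariate that is already there.

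**Working it through.** **Step 1: the plan's own figure.** Inputs from Sample size calculations: a 9-point difference, "assuming a SD of 24", "with 90% power and 5% Type I error". Sidedness is not stated; two-sided reproduces the figure.

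- Normal approximation: n per arm = 2 × (1.960 + 1.282)² × 24² / 9² ≈ 149.4, so 150.
- Exact noncentral t: 151 per arm, 302 in total, power 90.1%.
- Drop-out: 302 / 0.80 = 377.5, so 378.

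The plan's numbers reproduce. They use the unadjusted SD, so none depends on how NOSE is coded.

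**Step 2: how much of NOSE the bands keep.** Let R be the share of NOSE variance lying between bands. The documents do not give the NOSE distribution, so it is assumed, in 5-point steps from 30 to 100.

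- Uniform: the band means are 40, 65 and 90 around an overall mean of 65. Between-band variance = (25² + 0² + 25²) / 3 = 416.7. Total variance for 15 equally spaced values = 25 × (15² − 1) / 12 = 466.7. R = 416.7 / 466.7 = 0.893.
- Bell-shaped (discretised normal, nominal mean and SD): (60, 15) gives 0.795; (65, 17) 0.823; (70, 17) 0.819; (65, 20) 0.844.

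R is therefore about 0.80 to 0.89 in these cases.

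**Step 3: information gained from the exact score.** Let r be the correlation of baseline NOSE with 6-month SNOT-22. It is not given either; 0.2 to 0.4 is assumed, with a linear relation. The residual variance is 24²(1 − r²) with the exact score and 24²(1 − R r²) with bands, so

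gain = (1 − R r²) / (1 − r²) − 1, and equivalent participants = 302 × gain.

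| r | R | Calculation | Gain | Of 302 |
|---|---|---|---|---|
| 0.2 | 0.893 | 0.96428 / 0.96 − 1 | 0.45% | 1 |
| 0.3 | 0.80 | 0.928 / 0.91 − 1 | 2.0% | 6 |
| 0.4 | 0.893 | 0.85712 / 0.84 − 1 | 2.0% | 6 |
| 0.4 | 0.795 | 0.8728 / 0.84 − 1 | 3.9% | 12 |

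**Step 4: the same in power**, at 151 per arm for 9 points by normal approximation (unadjusted: 90.3%).

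- r = 0.2, R = 0.893: 91.3% with bands, 91.4% with the exact score.
- r = 0.3, R = 0.80: 92.3% and 92.7%.
- r = 0.4, R = 0.80: 93.7% and 94.5%.

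**Step 5: wider assumptions.** A narrower NOSE distribution (nominal mean 75, SD 10) brings R down to 0.69. Over R from 0.70 to 0.89 and r from 0.2 to 0.6, the treatment-effect variance is 0.4% to 17% larger with bands and the power difference is 0.1 to 1.8 points. The upper end needs both a strong correlation and a narrow distribution.

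**The case against.** The strongest objection is that the article never states the coding. The Randomisation section names the factor as severity with the NOSE score in brackets, the article condenses a fuller protocol, and covariate coding is often settled in a statistical analysis plan that is not shown. This stands in part: a reader might infer that the protocol fixes a bands-only model, and it does not say so. But NOSE appears as a stratification factor, blocked stratification needs discrete strata, the bands are said to be the ones used, and continuous use is flagged elsewhere in the same section. Bands are the natural reading, and adding the score is a concrete improvement rather than a request for missing detail.

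A reader might also infer that the trial's power depends on this adjustment. It does not. The plan calls its t test conservative because adjustment can only help, and the banded model still exceeds 90%.

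A third objection is that adjusting for stratification factors as randomised is a standard, valid analysis. That stands in full; within-band chance imbalance is ordinary sampling variation already reflected in the confidence interval.

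Fourth, the gain formula assumes linearity, while the plan itself allows for non-linear relations through fractional polynomials. If the relation is non-linear, a single linear term in place of the bands could do no better, or worse. That also stands, and it is why the score should be added to the bands rather than substituted for them.

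Finally, the secondary analysis of the same outcome already brings in continuous baseline SNOT-22. With that covariate in the primary model, the further gain from exact NOSE would shrink.

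**Conclusion.** The point holds as a minor efficiency improvement. As written, the primary model appears to use baseline NOSE in three bands although the exact score is available for everyone and severity is expected to matter most. The cost is about 0.5% to 4% of information, roughly 1 to 12 of 302 participants. This rests on three assumptions that the documents neither give nor rule out: a correlation of 0.2 to 0.4, bands that keep about 80% to 89% of NOSE variance, and a roughly linear relation.

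The documents do not support a stronger reading. The treatment effect is not biased, the type I error rate is not affected, and the 302, the 378 and the 90% power are all untouched.

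**What to change.** In the primary model, keep gender and the NOSE band used in randomisation, and add baseline NOSE as a continuous covariate, either linear or in a non-linear form fixed in advance. State this coding in the analysis section or the statistical analysis plan before outcomes are compared by arm. Keep the bands for randomisation, tabulation and subgroup display.

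The cost is one phrase, no new data, and one or two extra parameters. With an intercept, treatment, gender and two band terms, 302 − 5 = 297 residual degrees of freedom remain, so each added parameter costs roughly 1/297, or 0.3%, in precision. At the lowest assumed correlation that nearly cancels the gain; at the higher ones it is negligible beside it.

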#### Intervention – medical management

Patients randomised to the medical management arm will be asked to use a combination of an isotonic spray with a full twice-daily dose of a fluorinated steroid spray (mometasone furoate) which is a typical maximal medical therapy regime over a 6-month period. Preparatory work by the chief investigator indicated that most patients referred from their GP have never used this sustained combination therapy.

Sterimar Isotonic Nasal Spray dose: one spray (metred dose) into each nostril prior to using the Mometasone Nasal Spray.

Mometasone Nasal Spray dose: 100 mcg (two sprays) into each nostril twice daily for 6 weeks, followed by 100 mcg (two sprays) into each nostril once daily or 50 mcg (one spray) into each nostril twice daily for the remainder of the 6-month period.

Participants who wish to discontinue their allocated treatment, but remain in the trial, may access other treatments via the standard local NHS route. Such participants will be followed up as per their allocated treatment intervention arm. Participants in the surgical arm who wish to pursue medical treatment will not receive the trial Investigational Medicinal Product (IMP) prescription. Participants in the medical arm who wish to receive surgery and remain eligible for septoplasty should be added to the elective NHS waiting list.

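### Intention-to-treat is not bound to be conservative for septoplasty: stopped sprays, or nasal steroid added after surgery, move the difference towards surgery

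*Protocol article*

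**What the plan says.** The Primary outcome part of the Statistical analyses section makes intention-to-treat the basis of the primary analysis. It notes that participants may stop their allocated treatment and may in addition ask for a different one through the NHS. From these adjustments it concludes that "the intention-to-treat analysis will produce a conservative estimate of the effect of septoplasty". No condition is attached on which arm, or which kind of departure, is meant. The next sentence says that non-compliance may be handled by an as-treated or a CACE analysis. Both are optional.

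Other parts of the article bear on the claim:

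- **Active comparator.** Medical management is a six-month regimen of saline and mometasone sprays. The Background says such sprays may relieve blockage, and that their side effects may reduce compliance.
- **Spray use.** Under Medical management arm data, "Participant compliance with the IMP does not form part of the trial monitoring plan". Participants estimate at the 6-month visit how many bottles they used. The Discussion lists reliance on patient report as a limitation but gives no direction of bias.
- **Steroid after surgery.** Under Intervention – septoplasty, nasal steroid is not to be routine post-operative care, but any additional medication is recorded.
- **Leaving the allocated arm.** Under Intervention – medical management, in the paragraph on people who discontinue their allocation, "Participants in the surgical arm who wish to pursue medical treatment will not receive the trial Investigational Medicinal Product (IMP) prescription"; they may use ordinary NHS routes. Medical-arm participants who want surgery join the elective waiting list.

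**The concern.** The usual argument that intention-to-treat dilutes an effect fits a comparison with no treatment, or departures that consist only of switching arms. Here the comparator is itself a treatment that has to be taken daily. A medical-arm patient who stops the sprays and has no operation loses whatever the sprays gave, so the medical-arm mean worsens and the gap widens in favour of surgery. A surgical-arm patient who has the operation and then adds a nasal steroid may gain something beyond surgery alone, which also widens the gap. Neither is dilution, yet the sentence covers both.

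What is at stake is how a positive result is read. The trial is meant to inform guidance. A reader told that the estimate is conservative may take the observed difference as the least that septoplasty achieves over medical management used as specified, when part of it could reflect unused sprays.

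**Working it through.** **1. The plan's own figures.** Sample size calculations plans a superiority *t* test that takes the variance to be the same in both arms. Its error rates and spread are given as "with 90% power and 5% Type I error, assuming a SD of 24". The difference to be detected is 9 SNOT-22 points, which the article says needs 151 completers in each arm, 302 in all. On recruitment it says: "The target recruitment of 378 participants allows for 20% drop-out".

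- Normal approximation, two-sided: n per arm = 2 × 24² × (1.960 + 1.282)² / 9² = 149.4, so 150. The exact *t* test gives 151 per arm (power 0.901).
- Dropout: 302 / 0.8 = 377.5, so 378.
- A one-sided 5% test would need 122 per arm, so the stated figures are two-sided.

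The sample size reproduces and is not in question. It supplies the standard error of the difference: 24 × √(2/151) = 2.76 points.

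**2. A model for direction.** Let D be the advantage of surgery over sprays when both are used as specified, and m the benefit of sprays over nothing, both in SNOT-22 points. Treat effects as additive and assume that those who depart would have had the average benefit. Then

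ITT = D + a·m + d·e·m − b·D − c0·(m + D) − c1·D

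- a: share of the medical arm that stops sprays without surgery
- d and e: share of the surgical arm that adds nasal steroid after surgery, and the fraction of m they gain
- b: share of the medical arm that has surgery before 6 months
- c0: share of the surgical arm with no surgery and no other treatment
- c1: share of the surgical arm that uses sprays instead of surgery

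The first two departures carry a plus sign whenever m > 0. The other three carry a minus sign when D > 0.

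**3. Each route alone, with D = 9.** The article gives no value for m or for any rate; all are assumptions.

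| Departure | Term | Assumed rate | ITT, m = 4 | ITT, m = 9 |
|---|---|---|---|---|
| Stops sprays, no surgery | +a·m | 20% | 9.8 | 10.8 |
| Stops sprays, no surgery | +a·m | 40% | 10.6 | 12.6 |
| Adds steroid after surgery | +d·e·m | 20%, e = 0.5 | 9.4 | 9.9 |
| Medical arm crosses to surgery | −b·D | 10% | 8.1 | 8.1 |
| No surgery, no treatment | −c0·(m + D) | 10% | 7.7 | 7.2 |
| Sprays instead of surgery | −c1·D | 10% | 8.1 | 8.1 |

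With m = 0 the first three rows return 9.0, so these routes have no effect if the sprays do nothing.

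**4. Range for stopped sprays.** The shift is a·m. The smallest case is 0.10 × 3 = 0.3 points and the largest is 0.30 × 9 = 2.7 points. For comparison, 10% crossover to surgery removes 0.10 × 9 = 0.9 points.

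**5. Mixed cases, D = 9.**

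- 30% stop sprays, 20% add steroid (e = 0.5), 5% cross to surgery, 5% have neither surgery nor other treatment. For m = 4: 9 + 1.2 + 0.4 − 0.45 − 0.65 = 9.5. For m = 9: 9 + 2.7 + 0.9 − 0.45 − 0.9 = 11.25. Both exceed 9.
- 10% stop sprays, 20% cross to surgery, 10% have neither surgery nor other treatment. For m = 4: 9 + 0.4 − 1.8 − 1.3 = 6.3. For m = 9: 9 + 0.9 − 1.8 − 1.8 = 6.3. Both fall below 9.

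The sign depends on the mix.

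**6. Treatments equal when used as specified (D = 0).** For a shift x, the chance of a two-sided significant result is 1 − Φ(1.96 − x/2.76) + Φ(−1.96 − x/2.76). This is 8.4% at x = 1.5 and 16.5% at x = 2.7.

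**The case against.** **The sentence may mean crossover only.** It speaks of what is typical in surgical trials, which is ordinarily switching arms or not having the operation, and for those it is right. But the text before it names discontinuation first and alternative treatment as a further possibility, and the sentence after it counts receipt of the alternative as one kind of non-compliance among others. The wording does not confine the claim to switching.

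**The trial is pragmatic.** If the question is which strategy to offer, unused sprays are part of medical management as delivered, and the a·m term is not bias. This stands. It means that the 8.4% and 16.5% above must not be read as Type I error of the primary test. For the offered-strategy comparison they are the chance of detecting a real difference between strategies. They describe only the as-used reading, which is the reading that the word conservative invokes.

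**Surgical-arm use of nasal steroid.** A reader might infer that any such use inflates the difference and cite the rule that these participants get no trial prescription. The documents do not support that. The rule concerns people who give up their allocated treatment, and sprays in place of surgery dilute the difference. Only steroid added after an operation moves it towards surgery, and the protocol says this should not be routine.

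**The article already deals with non-compliance.** It offers as-treated and CACE analyses, collects bottle estimates and concomitant medication, and admits the limitation on spray use. None of this corrects the stated direction. A CACE analysis that defines receipt by surgery alone would leave spray stopping and added steroid unaddressed. Detailed compliance definitions may properly sit in an analysis plan that is not shown, so their absence here is no fault.

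**Conclusion.** The unconditional statement is wrong for two kinds of departure that the plan allows, and right for the others. It rests on the sprays having some benefit (m > 0), which the Background treats as possible.

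A reader might go further and conclude that intention-to-treat is anti-conservative overall. That does not follow. The article gives no spray benefit, stopping rate or crossover rate; the 2.7-point figure is the extreme corner of the assumed range; and plausible mixes fall on either side of the as-used effect. Stopping may also be commoner in people who were gaining little, which would shrink the shift. What is shown is that the net direction is unknown, with shifts from stopped sprays that could be smaller or larger than the dilution from modest crossover.

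The primary analysis, the sample size and the data collection are unaffected. The point bears on how a positive result may be described, and it should be corrected before results are interpreted.

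**What to change.** Replace the sentence with a statement that intention-to-treat estimates the effect of being offered each strategy, and that non-adherence may move this in either direction from the effect of the treatments used as specified. Do not interpret the estimate as a lower bound for septoplasty.

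Alongside the primary result, report by arm, from data the trial already collects:

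- spray use in the medical arm, from the bottle estimates at the 6-month visit;
- nasal-steroid use after surgery, from concomitant medication records;
- surgery not received in the surgical arm;
- surgery before 6 months in the medical arm.

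If a CACE analysis is done, define receipt in both arms (operation performed; sprays used) and not by surgery alone.

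The cost is one sentence, one table and one definition, with no new data. The drawback is that recalled bottle counts are imprecise, so any analysis that depends on them should be presented as approximate.
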